## Abstract

**Background:**

Although beneficial in clinical practice, the INtubate-SURfactant-Extubate (IN-SUR-E) method is not successful in all preterm neonates with respiratory distress syndrome, with a reported failure rate ranging from 19 to 69 %. One of the possible mechanisms responsible for the unsuccessful IN-SUR-E method, requiring subsequent re-intubation and mechanical ventilation, is the inability of the preterm lung to achieve and maintain an “optimal” functional residual capacity. The importance of lung recruitment before surfactant administration has been demonstrated in animal studies showing that recruitment leads to a more homogeneous surfactant distribution within the lungs. Therefore, the aim of this study is to compare the application of a recruitment maneuver using the high-frequency oscillatory ventilation (HFOV) modality just before the surfactant administration followed by rapid extubation (INtubate-RECruit-SURfactant-Extubate: IN-REC-SUR-E) with IN-SUR-E alone in spontaneously breathing preterm infants requiring nasal continuous positive airway pressure (nCPAP) as initial respiratory support and reaching pre-defined CPAP failure criteria.

**Methods/design:**

In this study, 206 spontaneously breathing infants born at 24^+0^–27^+6^ weeks’ gestation and failing nCPAP during the first 24 h of life, will be randomized to receive an HFOV recruitment maneuver (IN-REC-SUR-E) or no recruitment maneuver (IN-SUR-E) just prior to surfactant administration followed by prompt extubation. The primary outcome is the need for mechanical ventilation within the first 3 days of life. Infants in both groups will be considered to have reached the primary outcome when they are not extubated within 30 min after surfactant administration or when they meet the nCPAP failure criteria after extubation.

**Discussion:**

From all available data no definitive evidence exists about a positive effect of recruitment before surfactant instillation, but a rationale exists for testing the following hypothesis: a lung recruitment maneuver performed with a step-by-step Continuous Distending Pressure increase during High-Frequency Oscillatory Ventilation (and not with a sustained inflation) could have a positive effects in terms of improved surfactant distribution and consequent its major efficacy in preterm newborns with respiratory distress syndrome. This represents our challenge.

**Trial registration:**

ClinicalTrials.gov identifier: NCT02482766. Registered on 1 June 2015.

## Background

The pathogenesis of bronchopulmonary dysplasia (BPD) in preterm infants is multifactorial, but the role of ventilator-induced lung injury (VILI) is very important [1]. Although the respiratory support of preterm infants with respiratory distress syndrome (RDS) has improved and new modes of mechanical ventilation have been developed, the incidence of BPD has remained unchanged. Avoiding invasive mechanical ventilation by starting non-invasive respiratory support, such as continuous positive airway pressure (CPAP), in the delivery room is considered an important first step in reducing VILI and BPD. In case invasive mechanical ventilation is necessary, the recruitment of collapsed alveoli, thereby creating an optimal functional residual capacity (FRC) and limiting exposure to large tidal volumes and repetitive “opening and closing” of the unstable alveoli, may be the most effective way to reduce the risk of VILI and subsequent BPD.

The findings from the COIN [2], SUPPORT [3], and VON DRM [4] trials – comparing Early CPAP versus standard care (intubate, surfactant, mechanical ventilation) – are remarkably consistent. No single trial was able to demonstrate a statistically significant difference in the risk of death or BPD when infants were managed initially with CPAP compared to mechanical ventilation. From the results of these three studies, it is clear that initial stabilization on CPAP, and provision of rescue surfactant only when necessary, is at least as beneficial, and quite possibly preferred, over the standard therapy of intubation of all infants at risk in the delivery room and needing subsequent support with mechanical ventilation. The Italian Neonatal Network report of 2012 showed that an initial nasal continuous positive airway pressure (nCPAP) approach was used in approximately 60 % of cases, while Dargaville et al. [5] have reported that 50 % of newborns with gestational age (GA) 25–28 weeks were initially managed with nCPAP, substantially lower than the 65–90 % reported in other studies [6, 7]. The percentage of CPAP failure in the newborns of 25–28 weeks’ gestation is 45 % in the Australian experience [5], higher than that reported by Ammari et al. (25 %) [6] and similar to that reported by De Jaegere et al. (50 %) [7] and in the COIN trial (46 %) [2]. Therefore, the optimal respiratory care of newborn infants with RDS may involve yet another choice.


### Trial hypothesis

The primary hypothesis of this study is that there will be a reduction in the need of mechanical ventilation in the first 72 h of life (excluding the transient tracheal intubation performed for surfactant administration and the mechanical ventilation administered for lung recruitment) in spontaneously breathing infants born at 24^+0^–27^+6^ weeks’ gestation and failing nCPAP during the first 24 h of life who received an HFOV recruitment maneuver (IN-REC-SUR-E) compared to those receiving no recruitment maneuver (IN-SUR-E) just prior to surfactant administration followed by prompt extubation.

## Methods/design

### Study design

This will be an unblinded multi-center randomized trial of IN-REC-SUR-E versus IN-SUR-E in infants born at 24^+0^–27^+6^ weeks’ gestation.

### Inclusion criteria

Infants satisfying the following inclusion criteria will be eligible to participate: In-born at 24^+0^–27^+6^ spontaneously breathing at birth but requiring respiratory support (CPAP or O_2_) at 5 min of life Parental consent has been obtained Failing nCPAP during the first 24 h of life

### Exclusion criteria

 Severe birth asphyxia or a 5-min Apgar score <3 Endotracheal intubation in the delivery room for resuscitation or insufficient respiratory drive according to AAP guidelines [16]. Prolonged premature rupture of membranes (PROM) for more than 3 weeks Presence of major congenital malformations Hydrops fetalis Inherited disorders of metabolism

### Sample size

We hypothesized that a recruitment maneuver (in HFOV modality) before surfactant administration might decrease of the need of subsequent mechanical ventilation during the first 72 h of life from 50 % [2, 5, 7] to 30 %. We calculated that 103 newborns must be enrolled in each group to detect this difference as statistically significant with 80 % power at the 0.05 alpha level using the two-sided Pearson’s chi-square test.

### Randomisation

Infants will be allocated to one of the two treatment groups in a 1:1 ratio according to the minimization method, using an interactive web-based electronic system. Randomization will be stratified by center and gestational age (24^+0^–25^+6^ weeks or 26^+0^–27^+6^ weeks). A monthly accrual report about the study will be sent to the participating centers.

### Blinding

The study will not be blinded, and the staff performing the study also will take subsequent care of the infants.

### Management in the delivery room

Positive pressure with a neonatal mask and a T-piece system (Neopuff Infant Resuscitator ®, Fisher and Paykel, Auckland, New Zealand) will be used to stabilize the newborns after birth. All the neonates will receive one (or two) SLI maneuver(s) (25 cmH_2_O for 10–15 s) [14] and will be transferred to the NICU on nCPAP (6 cmH_2_O). If necessary, infants will start mechanical ventilation in agreement with the American Academy of Pediatrics’ guidelines on neonatal resuscitation [16]. In this latter case the babies will be excluded from the study (see Exclusion criteria section, page 4).

### CPAP failure criteria

In the NICU, nCPAP will be given through nasal prongs/mask using the standard method of the single centre (ventilator, flow-dependent system) with an initial pressure of 6 to 7 cmH_2_O, in all infants. CPAP failure is defined if they met any of the following criteria: FiO_2_ ≥ 0.30 on nCPAP [17] to maintain a SpO_2_ of 87–94 % [18] for at least 30 min unless rapid clinical deterioration has occurred; respiratory acidosis defined as pCO_2_ > 65 mmHg (8.5 kPa) and pH <7.20 on an arterial or capillary blood gas sample; apnea defined as more than four episodes of apnea per hour or more than two episodes of apnea per hour when ventilation with bag and mask will be required.

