### HFOV recruitment maneuver

Infants in the IN-REC-SUR-E group will undergo the following approach: after intubation, HFOV will be delivered with the ventilator available in each NICU. The following initial ventilator setting will be advocated: continuous distending pressure (CDP): 8 cmH_2_O; frequency: 10–15 Hz; ∆P: 15 cmH_2_O or amplitude 30 % eventually increased – chest to be “visibly vibrating”; I:E 1:2. ΔP (or amplitude) first and/or frequency will subsequently be adjusted to achieve a tidal volume (V_T_) of 1.5–2 ml/kg and/or to maintain the transcutaneous partial carbon dioxide pressure (TcPCO_2_) between 40 and 60 mmHg (5.3 and 8.0 kPa). The infants will be subjected to an open lung ventilation strategy aiming to recruit and stabilize the majority of collapsed alveoli/sacculi, using oxygenation as an indirect parameter for lung volume. Optimal recruitment is defined as adequate oxygenation using a fraction of inspired oxygen (FiO_2_) of 0.25 or less. Starting at 8 cmH_2_O, the CDP will be increased stepwise (2 cmH_2_O every 2–3 min) as long as pulse oximetry (SpO_2_) improves. The FiO_2_ will be reduced stepwise, keeping SpO_2_ within the target range (87–94 %). The recruitment procedure will be stopped if oxygenation no longer improves or if the FiO_2_ is equal to or less than 0.25. The corresponding CDP will be called the opening pressure (CDP_O_). Next, the CDP will be reduced stepwise (1–2 cmH_2_O every 2–3 min) until the SpO_2_ deteriorates (by at least 2–3 points). The corresponding CDP will be called the closing pressure (CDP_C_). After a second recruitment maneuver at CDP_O_ for 2 min, the optimal CDP (CDP_OPT_) will be set 2 cmH_2_O above the CDP_C_ for at least 3 min [19]. A chest radiograph at this point is advised.

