### Surfactant treatment

Infants in the IN-REC-SUR-E arm will undergo the following approach: as soon as possible after the recruitment maneuver (at CDP_OPT_) a dose of poractant alfa (Curosurf (Chiesi Farmaceutici, Parma, Italy)) of 200 mg/kg will be administered via a closed administration system in one to two aliquots (1–2 min). The tube position will be confirmed by auscultation. A temporary reduction of frequency may be necessary to increase the V_T_ up to 2.5 ml/kg for improving the surfactant spreading.

Infants in the IN-SUR-E arm will undergo the following approach: after intubation, a dose of poractant alfa (Curosurf (Chiesi Farmaceutici, Parma, Italy)) of 200 mg/kg will be administered via a closed administration system in one to two aliquots (1–2 min). The tube position will be confirmed by auscultation. During surfactant administration, infants will be manually ventilated to facilitate surfactant distribution. If necessary, mechanical ventilation with a peak inspiratory pressure (PIP) of 20–22 cmH_2_O, a PEEP of 5–6 cmH_2_O and a respiratory rate of 30–40 breaths/min will be subsequently started to achieve a V_T_ of 4–6 ml/kg and/or to maintain the transcutaneous partial carbon dioxide pressure (TcPCO_2_) between 40 and 60 mmHg (5.3 and 8.0 kPa).

After surfactant administration, the babies of both groups will be extubated within 30 min (if satisfactory respiratory drive is present) and will receive nCPAP (6–8 cmH_2_O) [20]. In case of insufficient respiratory drive, CDP and/or ΔP (in the babies of IN-REC-SUR-E arm) or PIP (in the IN-SUR-E arm) will be reduced until spontaneous respiratory activity is restored, to maintain the transcutaneous partial carbon dioxide pressure (TcPCO_2_) between 40 and 60 mmHg (5.3 and 8.0 kPa). Maintaining a FiO_2_ < 0.30 to obtain SpO_2_ values in the desired range (87–94 %) will drive the eventual reduction in the level of CPAP in the following days. The decision as to whether to begin bi-level nCPAP (BiPAP) or nasal intermittent MV (N-IMV) to prevent the need for re-intubation in infants of both groups will be up to the neonatologist on duty, and will be considered in the final analysis.

Infants of both groups can receive a subsequent dose of surfactant (100 mg/kg of poractant alfa) using the same method (IN-SUR-E or IN-REC-SUR-E) if they meet the CPAP failure criteria again during the following 12 to 24 h.

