### Primary outcome measure

The primary outcome is the need for mechanical ventilation within the first 3 days of life and, therefore, we consider IN-REC-SUR-E or IN-SUR-E a success if mechanical ventilation is not required and a failure if the infant needs mechanical ventilation in the first 72 h. Infants in both groups will be considered to have reached the primary outcome also when they are not extubated within 30 min after surfactant administration or when they meet the nCPAP failure criteria after extubation.

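### The pCO2 limit for CPAP failure is printed as 65 mmHg (8.5 kPa), but 65 mmHg is 8.67 kPa, so the threshold has two values

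*Protocol article*

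**What the plan says.** The protocol article, under CPAP failure criteria, lists three criteria (FiO2, acidosis, apnea) and requires only one of them: "CPAP failure is defined if they met any of the following criteria". The acidosis criterion reads "respiratory acidosis defined as pCO_2_ > 65 mmHg (8.5 kPa) and pH <7.20 on an arterial or capillary blood gas sample". The limit at issue is the pair "> 65 mmHg (8.5 kPa" in brackets. This is the only place where the pCO2 limit is given, and no section says whether the mmHg or the kPa figure governs.

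The criteria are then used in three places:

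- **Eligibility** (Inclusion criteria): "Failing nCPAP during the first 24 h of life".
- **Repeat surfactant** (Surfactant treatment): a further dose is allowed "if they meet the CPAP failure criteria again during the following 12 to 24 h".
- **Primary outcome** (Primary outcome measure): an infant also counts as having reached it "when they meet the nCPAP failure criteria after extubation".

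The only other carbon dioxide values given in both units are the transcutaneous targets under HFOV recruitment maneuver, "between 40 and 60 mmHg (5.3 and 8.0 kPa" in brackets, which recur under Surfactant treatment.

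**The concern.** A limit given in two units should be the same limit in both. Here the kPa figure is lower than the mmHg figure it is meant to restate, so a centre reading blood gases in kPa would declare CPAP failure at a lower pCO2 than a centre reading them in mmHg.

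The same criteria decide who enters the trial, who may be re-dosed and, in part, who has the primary outcome. Two infants with the same blood gas could therefore be classified differently according to the unit used at their centre.

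**Working it through.** **Inputs.** Printed limit: 65 mmHg and 8.5 kPa (CPAP failure criteria). Comparison pair: 40 and 60 mmHg, printed as 5.3 and 8.0 kPa (HFOV recruitment maneuver; Surfactant treatment). Conversion: 1 mmHg = 0.133322 kPa.

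**Step 1: does the factor reproduce the protocol's other figures?** Formula: kPa = mmHg × 0.133322.

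| mmHg | Exact kPa | To one decimal | Printed kPa | Printed minus exact |
|---|---|---|---|---|
| 40 | 5.333 | 5.3 | 5.3 | −0.033 |
| 60 | 7.999 | 8.0 | 8.0 | +0.001 |
| 65 | 8.666 | 8.7 | 8.5 | −0.166 |

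The first two rows reproduce and the third does not. The common shortcut of dividing by 7.5 does not rescue it: 65 / 7.5 = 8.667.

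**Step 2: could it be rounding?** Rounding to one decimal moves a value by at most 0.05 kPa. The discrepancy is 0.166 kPa, and 0.166 / 0.05 = 3.3 times that. Put the other way, values that round to 8.5 kPa lie from 8.45 to 8.55 kPa:

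- 8.45 / 0.133322 = 63.4 mmHg
- 8.55 / 0.133322 = 64.1 mmHg

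That interval excludes 65 mmHg.

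**Step 3: size of the gap.** 8.5 / 0.133322 = 63.755 mmHg. Then 65 − 63.755 = 1.245 mmHg, and 1.245 / 65 = 1.9%.

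**Step 4: who could be classified differently?** All of the following must hold together:

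- the centre applies the kPa figure;
- pCO2 is above about 63.8 mmHg and no higher than 65 mmHg;
- pH is below 7.20;
- neither the FiO2 nor the apnea criterion is met.

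For the primary outcome, the infant must also have been extubated within 30 min of surfactant and not otherwise need mechanical ventilation by 72 h. The document gives no pCO2 distribution, so the number of such infants cannot be calculated.

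**Step 5: effect on the comparison.** A unit convention would act at centre level, and "Randomization will be stratified by center and gestational age", so both arms at a centre would face the same limit. The sample size calculation uses event rates of 50% and 30% and does not involve the pCO2 figure.

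**The case against.** The strongest reply is that the intended limit is clear enough. The protocol always writes carbon dioxide values in mmHg first with kPa in brackets, and the mmHg figures are all round numbers. The natural reading is a 65 mmHg limit with a faulty conversion beside it. Nothing shows that any centre works in kPa, and if none does the effect is nil. Even if one does, several conditions must coincide before a single infant is affected, and no effect on the trial's result can be shown.

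Most of this stands, and it is why the point is minor. The format does favor mmHg, but it does not settle the matter, since 8.5 is also a round figure in kPa and no rule says which unit prevails. Nor does a small consequence make the printed figure right. The kPa value is there for readers who need it, and anyone who applies it uses a different limit.

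**Conclusion.** The concern holds. The printed kPa equivalent is wrong by 0.17 kPa (about 1.2 mmHg, 1.9% of the limit), and the threshold therefore has two values. Severity is minor.

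If every centre uses mmHg, no infant is affected. If some use kPa, few should be, because a low pH is also required and the other two failure criteria must be absent. That judgment of few is qualitative, as the document has no data from which to count them. No bias between arms is expected, on the assumption that the choice of unit is a feature of the centre and not of the treatment. Sample size and power do not change.

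**What to change.** Under CPAP failure criteria, replace 8.5 kPa with 8.7 kPa and add a short sentence saying that the mmHg value governs. The sentence deals with the small rounding difference that remains, since 8.7 / 0.133322 = 65.3 mmHg.

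Only if 8.5 kPa was the limit actually intended should the mmHg figure change instead, to 64 mmHg (64 × 0.133322 = 8.53 kPa). Nothing in the document points to that.

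The single limit should then apply wherever the criteria are used: eligibility, repeat surfactant and the primary outcome. The cost is one corrected figure and one sentence, with no change to design or analysis.

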### HFOV recruitment maneuver

Infants in the IN-REC-SUR-E group will undergo the following approach: after intubation, HFOV will be delivered with the ventilator available in each NICU. The following initial ventilator setting will be advocated: continuous distending pressure (CDP): 8 cmH_2_O; frequency: 10–15 Hz; ∆P: 15 cmH_2_O or amplitude 30 % eventually increased – chest to be “visibly vibrating”; I:E 1:2. ΔP (or amplitude) first and/or frequency will subsequently be adjusted to achieve a tidal volume (V_T_) of 1.5–2 ml/kg and/or to maintain the transcutaneous partial carbon dioxide pressure (TcPCO_2_) between 40 and 60 mmHg (5.3 and 8.0 kPa). The infants will be subjected to an open lung ventilation strategy aiming to recruit and stabilize the majority of collapsed alveoli/sacculi, using oxygenation as an indirect parameter for lung volume. Optimal recruitment is defined as adequate oxygenation using a fraction of inspired oxygen (FiO_2_) of 0.25 or less. Starting at 8 cmH_2_O, the CDP will be increased stepwise (2 cmH_2_O every 2–3 min) as long as pulse oximetry (SpO_2_) improves. The FiO_2_ will be reduced stepwise, keeping SpO_2_ within the target range (87–94 %). The recruitment procedure will be stopped if oxygenation no longer improves or if the FiO_2_ is equal to or less than 0.25. The corresponding CDP will be called the opening pressure (CDP_O_). Next, the CDP will be reduced stepwise (1–2 cmH_2_O every 2–3 min) until the SpO_2_ deteriorates (by at least 2–3 points). The corresponding CDP will be called the closing pressure (CDP_C_). After a second recruitment maneuver at CDP_O_ for 2 min, the optimal CDP (CDP_OPT_) will be set 2 cmH_2_O above the CDP_C_ for at least 3 min [19]. A chest radiograph at this point is advised.

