### Other collected data

The following data will be recorded for each infant: gestational age (GA), birth weight (BW), sex, Apgar score at 5 min, antenatal steroid treatment, prolonged PROM of more than 18 h, diagnosis of histological and/or clinical chorioamnionitis, type of delivery, clinical risk index for babies (CRIB) II score [22], occurrence of air leaks, pulmonary hemorrhage, patent ductus arteriosus (PDA) and need for surgical closure, timing of surfactant administration, grades 3–4 intraventricular hemorrhage (IVH) [23], periventricular leukomalacia (PVL) [24], higher than grade 2 retinopathy of prematurity (ROP) [25], necrotizing enterocolitis (NEC) [26], sepsis defined as a positive blood culture or suggestive clinical and laboratory findings leading to treatment with antibiotics for at least 7 days despite the absence of a positive blood culture, length of stay in the NICU, use of systemic postnatal steroids, and mortality. The discharge from NICU will be performed when infants will not need respiratory assistance other than using oxygen therapy and central venous catheter insertion.

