### Statistical analysis

The primary efficacy analysis will be conducted on an intention-to-treat basis. An as-treated analysis will also be implemented for secondary analyses if a large number of infants do not end up getting the treatment to which they were assigned. Clinical characteristics of infants in the “IN-REC-SUR-E” and “IN-SUR-E” groups will be described using mean values and standard deviation, median value and range, or rate and percentage. Univariate statistical analysis will be performed using the Student’s *t* test for parametric continuous variables, the Wilcoxon rank-sum test for non-parametric continuous variables, and Fisher’s exact test for categorical variables. A *p* value <0.05 will be considered statistically significant. Then, treatment arm and clinical characteristics which are most likely associated with the need for mechanical ventilation (gestational age, birth weight, antenatal steroids, CRIB score) will be included in a multiple logistic regression analysis to assess their independent role in predicting the clinical outcome. Effect estimates will be expressed as odds ratios (ORs) with maximum likelihood-based 95 % confidence limits. An interim analysis will be planned when 50 infants will be enrolled in each arm. The analysis will intend to compare treatment arms with respect to efficacy, safety, futility, assessment of difficulties with patient enrollment, and, if necessary, a sample size adjustment. In the interim analysis for safety the pre-specified stopping rules are: a mortality rate more than 40 %, a rate of severe IVH more than 30 % and a pneumothorax rate of more than 10 %. The interim-analysis will be performed by an independent statistician, blinded for the treatment allocation. The statistician will report to the independent Data and Safety Monitoring Board (DSMB). The DSMB will have unblinded access to all data and will discuss the results of the interim-analysis with the Steering Committee in a joint meeting. The Steering Committee will decide on the continuation of the trial and will report to the central Ethics Committee.

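### A chest radiograph is advised in the recruitment arm only, so pneumothorax, a safety stopping outcome, may be detected more readily there; record how each one was found.

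*Protocol article*

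**What the plan says.** The section *HFOV recruitment maneuver* applies to one arm: "Infants in the IN-REC-SUR-E group will undergo the following approach: after intubation, HFOV will be delivered with the ventilator available in each NICU". It ends, after the optimal continuous distending pressure (CDP_OPT) has been set, with the sentence "A chest radiograph at this point is advised". Surfactant follows.

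The section *Surfactant treatment* sets out the control procedure: "Infants in the IN-SUR-E arm will undergo the following approach: after intubation, a dose of poractant alfa" is given, with manual ventilation. No film is mentioned before or after. For each arm the same section says "The tube position will be confirmed by auscultation". The article mentions no other chest radiograph for either arm.

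*Other collected data* lists "occurrence of air leaks, pulmonary hemorrhage, patent ductus arteriosus (PDA) and need for surgical closure". *Data collection* says the data come from clinical records.

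Under *Statistical analysis*, "An interim analysis will be planned when 50 infants will be enrolled in each arm", and its stated aims include comparing the arms on safety. For safety, the limits that trigger stopping are these: "a mortality rate more than 40 %, a rate of severe IVH more than 30 % and a pneumothorax rate of more than 10" per cent. The section does not say whether these limits apply to each arm or to all infants together. *Blinding* states that the trial is open and that study staff also give the later care.

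**The concern.** Pneumothorax is a foreseeable harm of a stepwise pressure manoeuvre, so its comparison between arms has to be interpretable. A pneumothorax without clinical signs can be seen on the advised film in the recruitment arm. In the control arm, as the article describes it, no planned step at that point would show it, and it is counted only if some other film reveals it.

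The likely direction is over-detection after recruitment. Two errors could follow. An excess caused partly by imaging could count towards stopping an acceptable intervention. Or a real excess could be dismissed as a product of the extra film. If the data do not show how each leak was found, neither reading can be tested.

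**Working it through.** **The two procedures side by side, from the article**

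| Step | IN-REC-SUR-E | IN-SUR-E |
|---|---|---|
| After intubation | HFOV recruitment to CDP_OPT | surfactant |
| Chest film | advised at CDP_OPT, before surfactant | none described |
| Tube position | auscultation | auscultation |
| Air leak recorded | occurrence, from clinical records | the same |

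The only difference in opportunity for detection that the text creates is the advised film.

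**What the rule means in counts.** Inputs from *Statistical analysis*: 50 infants per arm at the interim, limit above 10 %.
- Per arm: 10 % of 50 is 5, so crossing needs at least 6 of 50.
- Pooled: 10 % of 100 is 10, so crossing needs at least 11 of 100.

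The article gives no expected pneumothorax rate and no crossing probability, so there is no stated figure to reproduce.

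**Illustration under assumed rates.** Let p be the rate found without the advised film (assumed 3 %, 5 % or 7 %). Let d be the net points that the film adds in the recruitment arm (assumed 0, 1 or 3). To count towards d, a leak must be present at CDP_OPT, clinically silent, and never found otherwise.
- Per arm, recruitment: P(X ≥ 6) = 1 − Σ C(50,x) q^x (1 − q)^(50−x) over x = 0 to 5, with q = p + d.
- Pooled: P(X + Y ≥ 11), with X ~ Binomial(50, p + d) and Y ~ Binomial(50, p).

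| Assumed p | d | Recruitment arm, ≥ 6 of 50 | Control arm, ≥ 6 of 50 | Pooled, ≥ 11 of 100 |
|---|---|---|---|---|
| 3 % | 0 | 0.4 % | 0.4 % | 0.02 % |
| 3 % | 1 point | 1.4 % | 0.4 % | 0.08 % |
| 3 % | 3 points | 7.8 % | 0.4 % | 0.5 % |
| 5 % | 0 | 3.8 % | 3.8 % | 1.1 % |
| 5 % | 1 point | 7.8 % | 3.8 % | 2.2 % |
| 5 % | 3 points | 20.8 % | 3.8 % | 6.0 % |
| 7 % | 0 | 13.5 % | 13.5 % | 9.1 % |
| 7 % | 1 point | 20.8 % | 13.5 % | 12.9 % |
| 7 % | 3 points | 38.4 % | 13.5 % | 22.9 % |

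The direction is the same under both readings of the rule. The effect is smaller when pooled, because only half of the infants are exposed to the extra detection.

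**The case against.** The strongest reply is that one optional film is not an ascertainment schedule. The article states no purpose for it, and a check of lung inflation is a natural reading. All the infants are very preterm, have failed nCPAP and have been intubated. Centres may image controls routinely, and the full protocol, which is not shown, may say so. The film precedes surfactant, whereas air leaks are recorded without restriction to the procedure, so many silent leaks would be found later in either arm. Crossing the limit does not stop the trial mechanically: the DSMB sees unblinded data and the Steering Committee decides. Any bias runs against the intervention.

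All of this stands as a limit on size. It does not remove the asymmetry, which the article itself writes into one arm for an outcome that it makes a stopping criterion. A DSMB with unblinded data still cannot separate imaging from harm if the mode of detection was not recorded.

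Three stronger readings are tempting but not supported:
- *That pneumothorax is actively sought in one arm, and that control leaks surface only on clinically indicated films.* The text shows a difference in opportunity. It is silent on how controls are imaged.
- *That leaks seen only on the CDP_OPT film should be left out of the stopping rate.* Such a leak may be a true harm of the manoeuvre, found when one would expect it. Removing it would weaken the rule in the arm that it should protect.
- *That the film gives the recruitment arm a different check of tube position, so that two sections conflict.* The same auscultation sentence is given for both arms and the film is not linked to tube position. There is nothing to reconcile.

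**Conclusion.** The point holds in limited form. Pneumothorax may be detected more readily in the recruitment arm, because the article advises a film there and describes none for controls. The size cannot be determined from the article. With a 5 % base rate and 1 to 3 extra points, the chance of crossing rises from 3.8 % to between 7.8 % and 20.8 % per arm, or from 1.1 % to between 2.2 % and 6.0 % pooled. These figures rest on assumed rates, on the advised film being taken often enough to add that many points, and on controls not being imaged equivalently at that stage. If centres image both arms alike, the difference shrinks towards zero. The film does not directly affect the primary outcome. What is at stake is whether a safety excess, at the interim or at the end, can be interpreted.

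**What to change.** 1. Keep every pneumothorax, however found, in the rate used for the interim safety rule.
2. Record for each event the timing and indication of the diagnosing film: advised CDP_OPT film, or clinically indicated or other.
3. Report to the DSMB, and in the final analysis, a second between-arm comparison limited to pneumothorax that was symptomatic, drained, or seen on a clinically indicated film. List leaks seen only on the CDP_OPT film separately.

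The cost is one eCRF field and one extra tabulation. No safety signal is removed, and no radiograph is added or withdrawn; whether to take one remains a clinical matter on which this point takes no view. The second comparison has one weakness: in an open trial, the decision that a film is clinically indicated may itself depend on the arm. It should therefore be read beside the full rate and not in place of it.
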